# 1. TRIAL SUMMARY

| **TITLE** | A randomised trial to determine the effectiveness of the Preparing For Life programme which aims to improve the school readiness skills of socioeconomically disadvantaged children in Dublin, Ireland |
| --- | --- |
| **OBJECTIVES** | **Primary objective**  To test the effectiveness of the Preparing for Life (PFL) programme at improving the school readiness skills and life outcomes of socioeconomically disadvantaged children.  **Secondary objective**  To test the effectiveness of the Preparing for Life (PFL) programme at improving parental skills and the quality of the home environment. |
| **DESIGN** | Randomised controlled trial |
| **SAMPLE SIZE** | 300 (100 in randomised high treatment group; 100 in randomised low treatment group and 100 in external comparison group) |
| **STUDY POPULATION** | Pregnant women residing in the PFL catchment area |
| **ELIGIBILITY CRITERIA** | **Inclusion criteria**   1. Women (age 16+) pregnant between 2008 and 2010 2. Residing in the PFL catchment area 3. Willing to be assigned to either of the study intervention groups 4. Written informed parental/carer consent   **Exclusion criteria**   1. Under the age of 16 2. Not pregnant 3. Not residing in the PFL catchment area 4. No written consent provided. |
| **TREATMENT** | **5 year home visiting mentoring programme & group Triple P parenting programme** |
| **PRIMARY ENDPOINT** | **School Readiness Skills** 1. Cognitive development: measured using Ages and Stages Questionnaire (at 6, 12, 18, 24, 36, 48 months); Developmental Profile 3 (at 12, 18, 24, 36, 48); British Ability Scales (at 48 months); Executive functioning & delay of gratification (48 months); Early Development Instrument- Short Form (at school entry). 2. Physical health and motor skills: measured using Ages and Stages Questionnaire (at 6, 12, 18, 24, 36, 48 months); hospital records (at 48 months); parent-reported child health (at 6, 12, 18, 24, 36, 48); Early Development Instrument- Short Form (at school entry). 3. Socio-emotional development: measured using Temperament and Atypical Behaviour Scale (at 12 months); Difficult temperament (at 6 & 12 months); ASQ-Socio-Emotional scale (at 6, 12, 18, 24, 36, 48 months); Brief Infant Toddler Social and Emotional Assessment (at 12, 18 24, 36 months); Early Development Instrument- Short Form (at school entry). 4. Behavioural skills: measured using Temperament and Atypical Behaviour Scale (at 12 months); Child Behaviour Checklist (at 18, 36, 48 months); Peer Problems and Prosocial Behaviour (at 48 months); Early Development Instrument- Short Form (at school entry). 5. Language development and emergent literacy: measured using Mac-Arthur Bates Communicative Development Inventories (at 12, 18, 24 months); Ages and Stages Questionnaire (at 6, 12, 18, 24, 36, 48 months); British Ability Scales (at 48 months); Early Development Instrument- Short Form (at school entry). |
| **SECONDARY ENDPOINTS** | 1. Birth outcomes: maternity hospital records at birth (birth weight, gestational age, prematurity, Apgar score). 2. Labour outcomes: maternity hospital records at birth (instrumental delivery, caesarean section- elective, emergency). 3. Parenting skills: Adult Adolescence Parenting Inventory (at baseline &12 months); Knowledge of Infant Development (at baseline & 12 months); Parental locus of control (at 6 months); Condon Maternal Attachment Scale (at 6 & 24 months); Parenting Stress Index (at 6, 24 & 48 months); Parenting Daily Hassles Scale (at 18, 36 & 48 months).; Maternal Separation Anxiety (at 18 months); Parental Cognitions and Conduct Towards Infant Scale (at 6 & 24 months); Parenting Styles and Dimensions Questionnaire (at 36 & 48 months); Parental Acceptance -Rejection Questionnaire (at 36 months).  4. Quality of the home environment: Home Observation for Measurement of the Environment scale (at 6, 18 & 36 months); Activities with child (at 6, 18, 36 months); Home Learning Environment (at 48 months); Material Deprivation scale (at 18 months); Framingham Safety Survey (at 6, 18, & 48 months); Family Environment Scale (at 12 &36 months); Difficult Life Circumstances (18 & 36 months); Neighbourhood Quality Evaluation Scale (at 36 months); Family Routine Inventory (at 36 months).  5. Parent health: physical health outcomes (self-reported) (at baseline, 6, 12, 18, 24, 36, 48 months); personality (Tem-Item Personality Inventory (baseline), Rosenberg self-esteem (at baseline12, 18, 48 months) Pearlin Self-Efficacy Scale (at baseline,12 & 48 months) ; Vulnerable Attachment Style Questionnaire (baseline); Considerations of Future Consequences (at baseline & 24 months); Future Outlook Inventory (at 12, 36 months); Self-control (at 18 months);  mental health outcomes (Edinburgh Postnatal Depression Scale at 6, 18, 24, 36, & 48); WHO-5 Index (at baseline, 6, 12, 36, 48) 6. Social support and service use: Level from support from various people (at 6, 18, 24, 36, & 48 months); community integration (at 6, 12, 18, 24, 36, 48 months); use of services (at 6, 18, 36 months); partner satisfaction (at 6, 12, 24, 48 months); Maternal Social Support Index ( at 18 & 36 month); Family Quality of Life (at 36 months); Relationship Quality Index (at 36 months). |

# 2. INTRODUCTION AND RATIONALE

Deprivation early in life has multiple long term consequences for both the individual and society in general. The consequences of being raised in disadvantaged circumstances are significant, as socioeconomic inequalities in children’s health and development emerge early and increase over time (Najman *et al*., 2004; Shonoff and Philipps, 2000). Growing up in poverty can affect a child’s early skill development leading to greater vulnerability at school entry (Duncan and Brooks-Gunn, 1997), poorer cognitive skills (Stipek and Ryan, 1997), less developed social skills (Janus and Duku, 2007), as well as more emotional and behavioural problems (McLoyd, 1998). In addition, such early developmental difficulties can also affect major long term public and social policy issues such as academic achievement (Raver, 2003), employment (Rouse, Brooks-Gunn and McLanahan, 2005), teenage pregnancy, and psychological well-being (Brooks-Gunn, 2003).

Such deprivation is intergenerational in nature and is difficult to eradicate. Remediation policies are the most common method for addressing social inequalities, yet evidence suggests that they are both costly and less effective than preventative policies (Carneiro and Heckman, 2003). An increasing body of evidence finds that targeted, early interventions aimed at at-risk children and their families can reduce socioeconomic disparities in children’s capabilities (see Sweet and Appelbaum, 2004 for a review). While a number of individual studies have found home visiting programmes to generate significant and positive short and long term outcomes (e.g. Olds et al., 1999;), a meta-analysis of home visiting programmes evaluated by experimental design found significant variation in programme effectiveness across studies (Sweet and Appelbaum, 2004). Much of this evidence is US based and there is a clear lack of research on the effects of early intervention in countries with different social and cultural contexts such as Ireland.

Investment in early intervention programmes is efficient from both biological and economic perspectives. Intervening early in life, when children are at their most receptive stage of development, has the potential to permanently alter their brain development and subsequent developmental trajectories (Halfon, Shulman, and Hochstein, 2001). Early intervention is also economically efficient. Research on US intervention programmes has demonstrated high rates of return such that the individual and societal benefits accrued from intervening early typically outweigh the costs (Karoly, Kilburn, and Cannon, 2005).

This study describes a randomised control trial (RCT) evaluation of a preventative programme which aims to improve the life outcomes of socioeconomically disadvantaged children. The programme will operate in several disadvantaged communities of Dublin with above national average rates of unemployment, early school leavers, lone parent households and social housing (Census, 2006). The *Preparing for Life* (PFL) programme works with families from pregnancy until school entry in order to promote positive child development through improved parental behaviour and social support.

# 3. AIMS, HYPOTHESIS and OBJECTIVES

**3.1 Aim**

To test the effectiveness of the Preparing for Life (PFL) programme at improving the school readiness skills and life outcomes of socioeconomically disadvantaged children.

**3.2 Primary hypothesis**

It is hypothesised that the children participating in Preparing for Life programme will be significantly better prepared for school than those in the low treatment group. The null hypothesis is that there will be no difference in school readiness skills between the high treatment and low treatment groups; this may arise if the intervention is not effective or if there is substantial contamination between groups.

**3.3 Secondary hypotheses**

To test the effectiveness of the Preparing for Life (PFL) programme at improving parental skills and the quality of the home environment.

# 4. OBJECTIVES

- To undertake a randomised controlled trial to evaluate whether, compared to the low treatment group, the PFL home visiting programme and group Triple P leads to improved school readiness skills among 4/5 year old children who are socioeconomically vulnerable.

- To use a quasi-experimental design to evaluate whether, compared to the external comparison group, the low treatment supports leads to improved school readiness skills among 4/5 year old children who are socioeconomically vulnerable.

# 5. OUTCOME MEASURES

**5.1 Primary endpoint**

*School Readiness Skills*

1. **Cognitive development**: measured using Ages and Stages Questionnaire (at 6, 12, 18, 24, 36, 48 months); Developmental Profile 3 (at 12, 18, 24, 36, 48); British Ability Scales (at 48 months); Executive functioning & delay of gratification (48 months) ); Early Development Instrument- Short Form (at school entry).
2. **Physical health and motor skills**: measured using Ages and Stages Questionnaire (at 6, 12, 18, 24, 36, 48 months); hospital records (at 48 months); parent-reported child health (at 6, 12, 18, 24, 36, 48); Early Development Instrument- Short Form (at school entry).
3. **Socio-emotional development**: measured using Temperament and Atypical Behaviour Scale (at 12 months); Difficult temperament (at 6 & 12 months); ASQ-Socio-Emotional scale (at 6, 12, 18, 24, 36, 48 months); Brief Infant Toddler Social and Emotional Assessment (at 12, 18 24, 36 months); Early Development Instrument- Short Form (at school entry).
4. **Behavioural skills**: measured using Temperament and Atypical Behaviour Scale (at 12 months); Child Behaviour Checklist (at 18, 36, 48 months); Peer Problems and Prosocial Behaviour (at 48 months); Early Development Instrument- Short Form (at school entry).
5. **Language development and emergent literacy**: measured using Mac-Arthur Bates Communicative Development Inventories (at 12, 18, 24 months); Ages and Stages Questionnaire (at 6, 12, 18, 24, 36, 48 months); British Ability Scales (at 48 months); Early Development Instrument- Short Form (at school entry).

**5.2 Secondary endpoints**

1. **Birth outcomes:** maternity hospital records at birth (birth weight, gestational age, prematurity, Apgar score).
2. **Labour outcomes:** maternity hospital records at birth (instrumental delivery, caesarean section- elective, emergency).
3. **Parenting skills:** Adult Adolescence Parenting Inventory (at baseline &12 months); Knowledge of Infant Development (at baseline & 12 months); Parental locus of control (at 6 months); Condon Maternal Attachment Scale (at 6 & 24 months); Parenting Stress Index (at 6, 24 & 48 months); Parenting Daily Hassles Scale (at 18, 36 & 48 months).; Maternal Separation Anxiety (at 18 months); Parental Cognitions and Conduct Towards Infant Scale (at 6 & 24 months); Parenting Styles and Dimensions Questionnaire (at 36 & 48 months); Parental Acceptance -Rejection Questionnaire (at 36 months).
4. **Quality of the home environment:** Home Observation for Measurement of the Environment scale (at 6, 18 & 36 months); Activities with child (at 6, 18, 36 months); Home Learning Environment (at 48 months); Material Deprivation scale (at 18 months); Framingham Safety Survey (at 6, 18, & 48 months); Family Environment Scale (at 12 &36 months); Difficult Life Circumstances (18 & 36 months); Neighbourhood Quality Evaluation Scale (at 36 months); Family Routine Inventory (at 36 months).
5. **Parent health:** physical health outcomes (self-reported) (at baseline, 6, 12, 18, 24, 36, 48 months); personality (Tem-Item Personality Inventory (baseline), Rosenberg self-esteem (at baseline12, 18, 48 months) Pearlin Self-Efficacy Scale (at baseline,12 & 48 months) ; Vulnerable Attachment Style Questionnaire (baseline); Considerations of Future Consequences (at baseline & 24 months); Future Outlook Inventory (at 12, 36 months); Self-control (at 18 months); mental health outcomes (Edinburgh Postnatal Depression Scale at 6, 18, 24, 36, & 48); WHO-5 Index (at baseline, 6, 12, 36, 48).
6. **Social support and service use:** Level from support from various people (at 6, 18, 24, 36, & 48 months); community integration (at 6, 12, 18, 24, 36, 48 months); use of services (at 6, 18, 36 months); partner satisfaction (at 6, 12, 24, 48 months); Maternal Social Support Index ( at 18 & 36 month); Family Quality of Life (at 36 months); Relationship Quality Index (at 36 months).

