**8. Flow Chart**

**9. STUDY POPULATION**

All pregnant women from the PFL catchment communities (defined by the Northside Partnership who will manage the intervention) are eligible to participate.

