**9.1 Eligibility criteria**

**Inclusion criteria**

1. Women (age 16+) pregnant between 2008 and 2010
2. Residing in the PFL catchment area
3. Willing to be assigned to either of the study intervention groups
4. Written informed parental/carer consent

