**Exclusion criteria**

1. Under the age of 16
2. Not pregnant
3. Not residing in the PFL catchment area
4. No written consent provided.

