**10. study Procedures**

**10.1 Recruitment**

Recruitment into the study will occur through one of two sources: 1) in the maternity hospital at the first booking visit or 2) self-referrals in the community. The recruitment process will involve substantial interactions and collaboration with the maternity hospitals in order to identify eligible women in a confidential manner. The hospital administrative staff will send the UCD evaluation team a weekly list stating the number of women from the *PFL* catchment area who are scheduled to have their first booking visit at the hospital the following week. The list will include the time and date of the visit, but for confidentiality reasons, no names or contact information will be included. The hospital staff will also flag the files of any eligible women on their computer system. By doing this, an alert will appear on the computer screen when the eligible women are booked into the clinic in the Outpatient Department (OPD). When this alert appears, the OPD staff will give the eligible women a *PFL* flier describing the programme and introduce them to the *PFL* recruiter who will be present in the waiting room of the clinic. The recruiter will then briefly explain the programme to the eligible participants and ask for their contact details. If the eligible participant is interested in learning more about the programme, the recruiter will take their contact details. Next, the recruiter will ring the potential participant later that day to set up a recruitment appointment to take place in the village centre or the family home. During the recruitment appointment, the recruiter will describe the study in detail and bring the eligible participant through the information and consent form. If the eligible participant agrees to join the study she will be asked to sign the consent form. The same process will be used for all 3 groups (high treatment, low treatment, and comparison).

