| Mother’s Relationship with and the Involvement of the Biological Father | X |  | X | X | X |  |  |  |
| Father’s Highest Education Level | X |  | X |  |  |  |  |  |
| Age Mother’s Partner Left Full-time Education | X |  | X |  |  |  |  |  |
| **Employment/ Income Information** | Maternal Grandfather’s Main Occupation | X |  |  |  |  |  |  |  |
| Maternal Grandmother’s Main Occupation | X |  |  |  |  |  |  |  |
| Mother’s Maternity Leave |  |  | X | X |  |  |  |  |
| Mother’s Work Status | X |  | X | X | X | X | X | X |
| Mother’s Occupation | X |  | X | X | X | X | X | X |
| Mother’s Work Hours | X |  | X | X | X | X | X | X |
| Mother’s Wage | X |  | X | X | X | X | X | X |
| Maternal Job Stability |  |  |  | X | X | X | X | X |
| Mother’s Unemployment Info (if applicable) | X |  | X | X | X | X | X | X |
| Indicator for Social Welfare Payments to Household | X |  | X | X |  |  |  |  |
| Indicator for Social Welfare Payments to Household – Detailed |  |  |  |  | X | X | X | X |
| Household Weekly Income | X |  | X | X | X | X | X | X |
| Family Finances |  |  |  |  |  |  | X | X |
| Perception oF Financial Difficulty/Economic Perceptions | X |  | X | X | X | X | X | X |
| Mother’s Saving Habits | X |  | X | X | X | X | X | X |
| Partner’s Work Status | X |  | X | X | X | X | X | X |
| Partner’s Occupation | X |  | X | X | X | X | X | X |
| Partner’s Work Hours | X |  | X | X | X | X | X | X |
| Partner’s Wage | X |  | X | X | X | X | X | X |
| Partner’s Job Stability |  |  |  | X | X | X | X | X |
| Father’s Unemployment Info (if applicable) | X |  | X | X | X | X | X | X |
| **Pregnancy** | Week of Pregnancy | X |  |  |  |  |  |  |  |
| Child Due Date | X |  |  |  |  |  |  |  |
| Maternity Hospital Mother Attending | X |  |  |  |  |  |  |  |
| Week Pregnancy Confirmed | X |  |  |  |  |  |  |  |
| Week of First Antenatal Visit | X |  |  |  |  |  |  |  |
| Indicator of Mother’s Intention to take Antenatal Classes | X |  |  |  |  |  |  |  |
| Indicator of Whether Pregnancy was Planned | X |  |  |  |  |  |  |  |
| Mother’s Reaction to Pregnancy | X |  |  |  |  |  |  |  |
| Mother’s Family’s Reaction to Pregnancy | X |  |  |  |  |  |  |  |
| Mother’s Health Supplement Use (separate questions for multi-vitamins, folic acid, iron, calcium) Before and During Pregnancy | X |  |  |  |  |  |  |  |
| **Category** | **Measure/Information Obtained** | **BL** | **3** | **6** | **12** | **18** | **24** | **36** | **48** |

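### Two scales measured only at baseline are listed as secondary endpoints, and week of entry is not used to protect the birth outcomes in the non-randomised comparison

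*Protocol*

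**What the plan says.** **Endpoint list.** Under parent health, Section 5.2 includes the Ten-Item Personality Inventory, marked as baseline, and the "Vulnerable Attachment Style Questionnaire (baseline"). The trial summary repeats both. Table 1 gives each a single mark, in the BL column.

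**Timing.** Section 10.4 places baseline data collection after consent and randomisation and before the programme starts. Section 10.3 has the woman trigger her own allocation, and Section 10.2 says parents are told the result.

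**Analysis.** Section 12.2 sets intention to treat as the primary analysis. It compares high with low treatment, and both programme groups together with the external group. It then applies a stepdown procedure to families of related outcomes with a 0.1 threshold.

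**Birth outcomes and entry.** Section 5.2 also lists "maternity hospital records at birth (birth weight, gestational age, prematurity, Apgar score"). Section 9 makes eligible "All pregnant women from the PFL catchment communities". The timing criterion in Section 9.1 is "Women (age 16+) pregnant between 2008 and 2010", and the exclusions add no gestational limit. Section 10.1 recruits "1) in the maternity hospital at the first booking visit or 2) self-referrals in the community", by the same process in all three groups. Table 1 records "Week of Pregnancy" and the due date at baseline. The protocol states no use of either for the birth outcomes.

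**The concern.** A secondary endpoint should be something the programme could change. A scale collected once, before the first home visit, cannot be changed by it. If the list is followed as written, a treatment effect is estimated for two such scales and a chance imbalance could be reported as an effect on parent health. If they enter a stepdown family with real outcomes, they can also trigger rejection of the joint null, or raise the bar for outcomes the programme might affect.

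The second issue concerns when observation starts. A woman who enters at 37 weeks or later can no longer deliver preterm. A woman who enters at 34 weeks cannot contribute a birth before 34 weeks. Between randomised arms this is balanced in expectation. Between the programme community and another community nothing balances it, and the group that enters later shows fewer preterm births and longer mean gestation whatever the programme does.

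**Working it through.** **1. Which listed endpoints are baseline-only?** Measures in Section 5.2 that have a baseline wave:

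| Measure | Waves in Section 5.2 | Measured after the programme starts? |
|---|---|---|
| Adult Adolescence Parenting Inventory | baseline, 12 | yes |
| Knowledge of Infant Development | baseline, 12 | yes |
| Parent physical health | baseline, 6 to 48 | yes |
| Ten-Item Personality Inventory | baseline | **no** |
| Rosenberg self-esteem | baseline, 12, 18, 48 | yes |
| Pearlin Self-Efficacy | baseline, 12, 48 | yes |
| Vulnerable Attachment Style Questionnaire | baseline | **no** |
| Considerations of Future Consequences | baseline, 24 | yes |
| WHO-5 | baseline, 6, 12, 36, 48 | yes |

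Exactly two are baseline-only, and Table 1 agrees on both.

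**2. What would testing them do?** The true effect on each is zero. If the two tests are independent (assumed):
- chance that at least one reaches unadjusted p < 0.1: 1 − 0.9² = 19%;
- at p < 0.05: 1 − 0.95² = 9.75%.

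The stepdown procedure would still hold its familywise rate, but two null members make it stricter. Illustration, assuming a family of eight real outcomes, independence and a 0.1 familywise level:
- first-step per-test level with 8 outcomes: 1 − 0.9^(1/8) = 0.0131;
- with 10 outcomes: 1 − 0.9^(1/10) = 0.0105.

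The protocol does not state family membership, so this applies only if families follow the Section 5.2 groupings.

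**3. Late entry in the randomised contrast.** Let f be the share entering at 37 weeks or later. The documents give neither f nor preterm rates. Assume 10% vs 5% preterm among women still at risk, 100 per arm, two-sided 0.05 and the pooled-variance normal approximation. Without restriction the rates become 10%(1 − f) and 5%(1 − f) with 100 per arm. With restriction the rates stay at 10% and 5% with 100(1 − f) per arm.

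| f | Power, all women | Power, below 37 weeks only | n per arm for 80% power, all women |
|---|---|---|---|
| 0 | 26.7% | 26.7% | 435 |
| 10% | 24.4% | 24.5% | 487 (× 1.12) |
| 20% | 22.0% | 22.3% | 553 (× 1.27) |

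Restriction gains at most about 0.3 points. Power is low at f = 0 already, so late entry is not what limits this endpoint.

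**4. Late entry in the external contrast.** Suppose the preterm rate is 10% in both communities among women entering before 37 weeks, there is no programme effect, and a share g of one group only enters at 37 weeks or later (all assumed). The observed rate in that group is 10%(1 − g):
- g = 5%: 9.5%, a spurious difference of 0.5 points;
- g = 10%: 9.0%, 1 point;
- g = 20%: 8.0%, 2 points.

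The difference favours whichever group enters later. Differences in entry week below 37 add to it, so the cut-off alone is not enough and risk must start at entry. With equal entry weeks the bias is zero.

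**The case against.** **On the scales.** Both are openly marked as baseline in the list, Section 10.4 puts baseline before the programme, and Section 12.2 plans moderator modelling. A careful analyst would probably not report an effect on them. That limits the likely harm, but the list still calls them endpoints and nothing in the protocol takes them out of testing.

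**On gestation.** Several points stand. The hospital route recruits at the first booking visit, and Section 7.3 puts the first antenatal appointment at 12 weeks, so most entry may be early. Birth outcomes fall outside the aims in Sections 3 and 4, and the quasi-experimental objective there concerns school readiness. The same recruitment process serves all groups. Covariates for secondary endpoints are commonly left to the analysis plan, which Section 12.2 promises. This part is therefore a precaution. It survives because an identical process in a different community does not guarantee identical entry weeks, and Section 12.2 applies the external comparison to all analyses.

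**Stronger readings that are not supported.**
- A reader might infer that late entry biases the randomised comparison. It does not: entry week precedes randomisation, and intention to treat among all who join is a legitimate estimand. For birth weight and gestational age, late entry means little exposure, not impossibility of effect.
- A reader might infer a large loss of sample size from 1/(1 − f)². That formula holds the variance fixed. For a binary outcome with no events among late entrants the variance falls too: at f = 20% it gives 1.56, against about 1.27 under the rates assumed above.
- A reader might estimate average prenatal exposure. The documents give no distribution of entry weeks from which to do so.

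**Conclusion.** The classification error is definite and rests on no assumption about recruitment: two scales measured before the programme begins are listed as secondary endpoints and cannot show its effect. A difference between the randomised arms on them would be chance or, because baseline follows disclosed allocation, reporting. A difference from the external group could also reflect how the two communities differ beforehand. The 19% figure assumes independent, unadjusted tests at 0.1.

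The gestational point is secondary and conditional. It concerns the non-randomised comparison with the external group, where unequal entry weeks would bias prematurity and gestational age. The documents show neither that entry weeks will differ nor by how much. In the randomised contrast the consequence is dilution of unknown size. The primary school-readiness endpoint is not affected.

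**What to change.** 1. In Section 5.2 and the trial summary, remove the Ten-Item Personality Inventory and the Vulnerable Attachment Style Questionnaire from the secondary endpoints. List them as baseline characteristics or moderators, and state that they belong to no outcome family in the stepdown procedure.
2. For the comparison with the external group, report week of pregnancy at entry by group. Count prematurity only among women below 37 weeks at entry, with the risk period starting at entry. Adjust the other birth outcomes for entry week.
3. In the randomised contrast, keep all women under intention to treat. Reporting entry week by arm is enough there; a restricted prematurity analysis would be valid but adds almost no power.

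**Cost.** Wording only, since week of pregnancy and due date are already collected at baseline. Women entering at 37 weeks or later leave the external prematurity comparison, where they carry no information.
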